## Abstract

People with multiple myeloma (MM) are second only to people with lung cancer for the poorest reported health-related quality of life (HRQoL) of all cancer types. Whether exercise can improve HRQoL in MM, where bone pain and lesions are common, requires investigation. This trial aims to evaluate the efficacy of an exercise intervention compared with control on HRQoL in people with MM. Following baseline testing, people with MM (*n* = 60) will be randomized to an exercise (EX) or waitlist control (WT) group. EX will complete 12-weeks of supervised (24 sessions) and unsupervised (12 sessions) individualized, modular multimodal exercise training. From weeks 12–52, EX continue unsupervised training thrice weekly, with one optional supervised group-based session weekly from weeks 12–24. The WT will be asked to maintain their current activity levels for the first 12-weeks, before completing the same protocol as EX for the following 52 weeks. Primary (patient-reported HRQoL) and secondary (bone health and pain, fatigue, cardiorespiratory fitness, muscle strength, body composition, disease response, and blood biomarkers) outcomes will be assessed at baseline, 12-, 24- and 52-weeks. Adverse events, attendance, and adherence will be recorded and cost-effectiveness analysis performed. The findings will inform whether exercise should be included as part of standard myeloma care to improve the health of this unique population.

## 1. Introduction

Recent remarkable advances in treatments for people with multiple myeloma (MM), an incurable cancer of plasma cells, are contributing to longer life expectancies [1]. However, the inevitable relapse and substantial disease- and treatment-related side effects can reduce patients’ health-related quality of life (HRQoL). In a recent population-wide study, people with MM had the most functional limitations and were second only to lung cancer for the highest psychological distress and lowest quality of life of all cancer types [2]. HRQoL has been shown to correlate with all-cause mortality in all disease stages of MM [3,4,5,6,7].

Exercise has been shown to be an effective therapy for improving HRQoL in other cancer patient populations both during and following treatment [8]. However, whilst these short-term benefits of exercise have been consistently reported, the maintenance of these benefits beyond the completion of interventions is understudied. In people with MM, only one intervention published as a single arm study [9] and later a randomized controlled trial [10] has explored the effects of aerobic and/or resistance exercise on HRQoL. The randomized controlled trial failed to find any effect of exercise on HRQoL. The lack of effect may be explained, at least in part, by low attendance to the prescribed intervention, i.e., once-weekly group classes at a hospital outpatient gym (only 80% attending >50% of sessions) and twice weekly home-based exercise (completion rates not reported). Adherence to the prescribed protocol was not reported for either the supervised or unsupervised sessions. Thus, the exercise dose received was lower than that prescribed and potentially insufficient to elicit benefits to HRQoL. Individualized supervised exercise sessions have been found to result in greater adherence and better outcomes compared with unsupervised/home-based sessions for people with cancer [11]. Therefore, future research is required which investigates the effect of an individualized supervised exercise intervention on the HRQoL of people with MM.

Cancer-related fatigue, decreased physical functioning, and breathlessness are experienced with very high incidence and severity among people with MM, contributing to poor HRQoL [12]. Whilst aerobic exercise has been found to effectively reduce fatigue, enhance physical functioning, and increase cardiorespiratory fitness in other cancer populations [13], several randomized controlled trials [10,14,15] exploring its efficacy on these outcomes in patients with MM found no significant improvements. The aerobic exercise in these studies was prescribed at a moderate intensity. High intensity interval training (HIIT) has been shown to elicit greater improvements in cardiorespiratory fitness in a shorter amount of time compared with moderate intensity aerobic exercise in other populations [16,17]. HIIT has also been found to be as effective as, if not superior to, moderate intensity aerobic exercise for improving body composition [18,19] and fatigue [20], whilst also helping cancer survivors maintain their motivation to exercise [21]. Two studies have investigated the effect of HIIT in people with hematological cancers which included people with MM in the study cohort [22,23]. However, despite showing that it was safe and feasible in this cancer population, there was no separate analysis for MM. Whether HIIT provides a feasible, effective, and time-saving training strategy to enhance cardiorespiratory fitness and physical functioning and reduce fatigue in patients with MM warrants investigation.

Exercising in the presence of bone lesions has been identified as a major safety concern by hematologists [24] and patients [25] alike, particularly during resistance training and impact loading activities. Bone involvement occurs more frequently in MM than in any other cancer [26], with up to 85% of patients with MM developing lytic lesions during the course of their disease [27]. Bone pain is commonly experienced in people with MM, with 45% experiencing bone pain in the vertebrae and 27% experiencing bone pain in other sites, such as the ribs and pelvis [25]. Reductions in bone mineral density and degradation of bone microarchitecture are frequent manifestations in people with MM due to inflammation secondary to myelo-suppressive treatments [28]. Prolonged periods of bed rest after autologous hematopoietic stem cell transplantation, high doses of steroids, nausea, and appetite loss can all have detrimental effects on total body and muscle mass [29,30,31], with the potential to contribute to cancer cachexia. Combined with an older average age at diagnosis (70 years) and high rates of peripheral neuropathy, people with MM are at a greater risk of falls and fractures. Combined resistance training and impact loading have been found to improve bone health, muscular strength, and balance, and thus quality of life in other populations [32,33,34]; further research is required to confirm its safety and efficacy in people with MM.

Whilst the short-term benefits of exercise on HRQoL in cancer survivors have been consistently reported [35], the maintenance of these benefits beyond the completion of interventions is often understudied. A recent systematic review showed that the increases in physical activity during exercise interventions are not maintained six months after intervention cessation in community-dwelling older adults [36]. Conversely, a systematic review of exercise interventions for women with breast cancer [37] found small improvements in physical function and fatigue still evident at long-term (≥6 months) follow-up; albeit only nine studies were found. Further investigation of the long-term maintenance of physical activity and psychosocial health benefits following exercise interventions is clearly required.

We aim to investigate the influence of an individualized supervised exercise intervention on HRQoL in people with MM compared with usual care. The effects of exercise on outcomes that may influence HRQoL (i.e., fatigue, bone pain, cardiorespiratory fitness, bone health, muscle strength, body composition, and balance), as well as the influence of exercise on markers of bone turnover, adipokines, immune functioning, and metabolomics will be compared with usual care. Adverse events, attendance, and adherence will be recorded and a cost-effectiveness analysis performed. Finally, after twelve weeks of supervised exercise and a further twelve weeks of a stepped-down supervision approach, the maintenance of the effect of exercise six months after cessation of all exercise support will be explored. It is hypothesized that a 12-week supervised exercise intervention will improve HRQoL, and factors that influence HRQoL, in people with MM compared with usual care. Exercise is also hypothesized to improve markers of bone turnover, adipokines, immune functioning, and metabolomic profiles compared with usual care. These effects are hypothesized to return to baseline levels six months after cessation of all exercise support.

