#### Stepped Down Supervision Approach

The modular multi-modal exercise program should be undertaken three times per week. For the first twelve weeks, two exercise sessions per week will be supervised by an AEP and once at home. For home-based sessions, elastic resistance bands will be provided, with advice for the purchase of dumbbells of appropriate weight. High intensity training will be replaced by a moderate intensity walk three times per week if a bike or treadmill is unavailable. Exercise supervision in the following three months will be stepped down to home-based sessions, with an optional weekly group class (2 to 6 participants) supervised by the study AEP. In addition, the AEP will telephone participants every two weeks to check on their adherence, any adverse events, prescribe progressions/regressions as appropriate, and answer any questions. Motivational interviewing will be used if any barriers are expressed. Following the first six months, all participants will be encouraged to maintain three exercise sessions per week for a further six months without group sessions. At the completion of their study involvement, participants will receive education regarding the Australian Government Department of Health Chronic Disease Management Plan, with no direct referrals to exercise physiologists or group classes.

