## 5. Statistical Considerations and Data Analyses

A priori power calculations determined that a sample of 44 participants (*n* = 22 per group) will be needed to detect a mean difference of 6.7 points [51] between groups on the EORTC QLQ-C30 MY20 after the 3-month supervised exercise phase, with 80% power and 5% alpha. To account for an anticipated dropout rate of 25%, 60 participants will be recruited to the study. A difference of 6.7 on the physical function subscale of the EORTC QLQ-C30 MY20 questionnaire, determined by receiver operating characteristic curve analysis, corresponds to the minimum clinically meaningful change considered important by people with MM [51].

Data will be analyzed using the Stata statistical software package (version 15.0, StataCorp, College Station, TX, USA). Data entry will be performed in duplicate, and accuracy will be assessed with automatic cross-checking procedures. Range checks for data values will be performed to promote data quality. Data will be assessed for normality using the Shapiro–Wilk test. Subsequent analyses will include standard descriptive statistics, *t* tests, correlation, regression, and one-way repeated measures ANOVA or the comparable non-parametric test as necessary to examine differences among timepoints. Each model will include covariates, as appropriate, and will be adjusted using the baseline value as a fixed continuous covariate. For accelerometer data, means and 95% confidence intervals will be calculated and repeated measures accounted for across multiple days within participants. Quality of life questionnaire items will be analyzed using random effects mixed modelling with Fisher’s least significant difference tests for post hoc analyses to compare mean changes in outcomes between groups at each assessment period, with time and group as the fixed factors. A time × group interaction term will be used to formally test for differences between groups (alpha = 0.05).

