The number of participants who provide data at each timepoint will be reported, with reasons as to why participants did not attend. Incomplete data and missing values will primarily be managed using intention-to-treat analyses, using a 70% cut-point for adherence. To ensure the robustness of the findings, a secondary sensitivity analysis will be performed [109]. Non-continuous data will be analyzed using multinomial logistic regression. Metabolomics and lipidomics data will be evaluated using multivariate statistics, including principal component analysis and sparse partial least squares discriminant analysis. The blood molecular time-series measures will be analyzed to determine the metabolic and immune pathways altered by exercise and to determine biomarkers of responders for physical fitness, fatigue, and pain, if any. Exercise and control groups will be further stratified by therapy and remission duration. All tests will be two-tailed, and an alpha level of 0.05 will be applied as the criterion for statistical significance. There are no interim analyses planned or early trial termination guidelines.

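### The exploratory month-12 hypothesis predicts no difference from baseline, but only difference tests are described, so a non-significant result could be mistaken for a return to baseline

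*Protocol article*

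**What the plan says.** The Introduction sets maintenance as an exploratory aim: "the maintenance of the effect of exercise six months after cessation of all exercise support will be explored". It then predicts the result: "These effects are hypothesized to return to baseline levels six months after cessation of all exercise support".

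Section 5 gives the tools. Timepoints are compared by "one-way repeated measures ANOVA or the comparable non-parametric test as necessary to examine differences among timepoints". The quality-of-life questionnaires go into a mixed model with Fisher's least significant difference tests, to "compare mean changes in outcomes between groups at each assessment period, with time and group as the fixed factors". For all of this, "All tests will be two-tailed, and an alpha level of 0.05 will be applied as the criterion for statistical significance". No margin or other criterion for a return to baseline is stated.

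On exposure in the second half of the year, the Stepped Down Supervision Approach section says: "Following the first six months, all participants will be encouraged to maintain three exercise sessions per week for a further six months without group sessions". Table 1 ticks adherence at 3 and 6 months and not at 12. Its footnote c says adherence is monitored continuously through the supervised and unsupervised intervention. According to the Abstract, the waitlist arm follows the same 52-week programme after its 12-week wait.

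**The concern.** A difference test can reject equality with baseline but cannot establish it. When the hypothesis is itself equality, every loss of precision (small numbers, dropout, variable scores) makes the predicted result more likely. The time × group term does not help at month 12, because by then both arms have been offered exercise. What remains is a within-person comparison.

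Maintenance is also taken up in the Discussion and Conclusions. The practical risk is a report that benefit disappears once support ends, when a meaningful part of it was kept. The Introduction describes relapse in this disease as inevitable, so even a real fall towards baseline could come from disease course, from stopping exercise, or from both. How much participants trained in months 6–12 therefore matters for interpretation, and the document is unclear on whether that is recorded.

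**Working it through.** **1. The plan's own figure.** Section 5 states that "a sample of 44 participants (*n* = 22 per group) will be needed to detect a mean difference of 6.7 points", with 80% power and 5% alpha at 3 months. No SD is given. Solving the two-sample t-test for the SD (difference 6.7, 22 per group, two-sided 0.05, power 0.80) gives 7.75; the normal approximation gives 6.7 / [(1.960 + 0.842) × √(2/22)] = 7.93. The dropout step gives 44 / 0.75 = 58.7, so 59, stated as 60.

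**2. Chance of a non-significant month-12 test when benefit is retained.** Paired t-test of month 12 against baseline, two-sided 0.05. The noncentrality is δ / (SD/√n), with n − 1 degrees of freedom.

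- Assumed: n = 22 (one arm) or 44 (both arms, each against its own pre-exercise baseline), taken from the plan's evaluable numbers.
- Assumed: δ = 3.35, half of 6.7.
- Assumed: SD of change from 7.75 to 20. The lower end borrows the SD implied by the 3-month calculation; the document gives no within-person SD of change.

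Example, n = 22, SD 12: standard error 12/√22 = 2.56, noncentrality 3.35/2.56 = 1.31, critical t = 2.08, power 0.24, so 76% non-significant.

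| SD of change | n = 22, 3.35 retained | n = 22, all 6.7 retained | n = 44, 3.35 retained | 95% CI half-width, n = 22 |
|---|---|---|---|---|
| 7.75 | 51% | 3% | 20% | 3.4 |
| 12 | 76% | 30% | 56% | 5.3 |
| 15 | 83% | 48% | 70% | 6.7 |
| 20 | 88% | 68% | 81% | 8.9 |

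Only at the most favourable SD does the one-arm test reliably detect even a fully retained benefit.

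**3. How often an interval rule could confirm a return.** With n = 22 and a true change of exactly zero, the simulated chance that the whole 95% CI lies within ±6.7 is about 42% at SD 12 and 11% at SD 15. The rule is honest but often indecisive.

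**4. Months 6–12, side by side.**

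- Table 1: adherence ticked at 3 and 6 months only.
- Footnote c: continuous monitoring through the unsupervised intervention.
- Abstract: unsupervised training runs from week 12 to week 52.
- Section 3.3.1 (Qualitative Analysis): the unsupervised intervention lasts 3 months, and Table 1 puts the interviews that follow it at 6 months.
- Cost-Effectiveness Analysis: the unsupervised phase lasts 6 months.
- Collection methods: the exercise physiologist keeps adherence records at supervised sessions and participants self-report the weekly home session (3.3.2); two-weekly calls are described for the three months after week 12 (Stepped Down Supervision Approach).

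Whether footnote c reaches months 6–12 depends on which definition applies, and no collection method is described for that period.

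**The case against.** A reader might infer that the trial will treat a non-significant month-12 test as confirmation. The document does not say so. It lists analyses and an alpha level without a rule for interpreting maintenance, and an analysis plan not shown could supply one. That objection stands, so the point is about what the stated tests can support.

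A reader might also infer that no adherence is collected after month 6. Footnote c tells against this. Read with the Abstract, it covers the whole period to week 52. What stands is an inconsistency to reconcile.

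Nor can it be said that the aim is unanswerable. It is exploratory. Outcomes, disease status, self-reported activity and accelerometry are all scheduled at 12 months, and both relevant changes can be estimated from planned visits. Baseline is a legitimate reference for a return-to-baseline hypothesis; the week-24 to week-52 change adds to it and does not replace it.

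Two further objections limit the remedy. The 6.7 points are cited for the physical function subscale, whereas the primary outcome is the QLQ-C30 summary score and the hypothesis also covers fitness, bone and blood markers, so one margin cannot serve them all. And a split by continued training is confounded, since relapse can itself stop training.

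The objections do not remove the mismatch. The article itself fixes both the hypothesis and the family of tests.

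**Conclusion.** The concern holds in limited form. The hypothesis is one of no difference, the described tests can only show a difference, no criterion for return is given, and no unexposed comparator remains at month 12. A non-significant result would therefore be weak evidence of return: a half-retained benefit is missed 51–88% of the time with 22 participants and 20–81% with 44. These figures rest on assumed SDs of change between 7.75 and 20 and on the planned evaluable numbers being reached at month 12. The adherence point is one of unclear and differing text. The 3-month primary comparison is unaffected. The change is worth making because it is cheap and guards a stated aim against a predictable misreading.

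**What to change.** 1. Report the week-52 minus baseline change and, in addition, the week-24 to week-52 change, each with a 95% CI. State that non-significance will not be read as return to baseline.
2. For the HRQoL outcome, claim return only if the CI lies within a margin pre-stated for that score; otherwise report not determined. If 6.7 is used for the summary score, justify it, since it is cited for the physical function subscale.
3. Pool both arms on time since starting exercise to gain precision, with the waitlist arm's repeated baseline battery (Table 1, footnote a) as its starting point.
4. Reconcile Table 1's adherence row with footnote c and with the three lengths given for the unsupervised phase. Collect a simple home-session log for months 6–12 at the existing 12-month visit.
5. Present change by continued training and by disease status descriptively only, without attributing it causally to loss of support.

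Cost: wording changes, one self-completed log and a small participant burden. The main downside is that not determined is a likely result if the SD is large.

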## 2. Methodology

This trial was prospectively registered on 12 March 2019 with the Australian New Zealand Clinical Trial Registry 12619000387123. (Protocol version 6, dated 19 March 2020) (http://www.anzctr.org.au/Trial/Registration/TrialReview.aspx?id=376687&isReview=true— accessed 1 October 2021). Trial registration includes all components of the World Health Organization Trial Registration Data Set, as recommended by the International Committee of Medical Journal Editors. A SPIRIT (Standard Protocol Items: Recommendations for Interventional Trials) checklist [38] is provided in File S1.

### 2.1. Trial Design and Setting

The study design is depicted in Figure 1. People diagnosed with MM will be invited to participate in this multi-site, single blind, randomized waitlist-controlled trial. A waitlist control group design was chosen to reduce participant dropout from a non-exercise control group [39]. Participants randomized to the waitlist control group will be encouraged to maintain their customary physical activity during the 3-month wait period.

The exercise program follows a stepped down supervisory approach with reduced supervision after three months. All participants will complete an assessment battery (see Table 1) at baseline, at the end of the supervised phase, and at 6- and 12-months following baseline testing (see Figure 1).

### 2.2. Participants

Men and women diagnosed with multiple myeloma will be invited to participate.

Inclusion criteria

i≥18 years old;iiDiagnosis of MM;iiiFree of any musculoskeletal, neurological, respiratory, metabolic, or cardiovascular conditions that may prevent safe completion of the exercise demands of the study;ivAble to give informed consent; andvAble to attend participating sites across southeast Queensland, Australia, to complete exercise training sessions and The University of Queensland for the testing sessions.

Exclusion criteria

iAbnormal resting electrocardiogram (ECG) with changes that suggest increased risk of exercise-induced cardiac event;iiUnstable angina;iiiCognitive impairment that impedes the ability to complete questionnaires; andivAny intellectual or physical disability which would make participation in an exercise intervention unsafe for the individual.

Interested participants will be individually interviewed using a medical history form and will be required to obtain their doctor’s approval prior to participating in the study. Individual participants will be discontinued from the trial, in agreement with their doctor where appropriate, if any major surgery or health condition arises that will significantly affect their safety to participate in exercise for a duration of >one month, or if the participant elects to withdraw their consent for any reason.

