### 3.1. Primary Outcome

#### Cancer-Specific Quality of Life (EORTC QLQ-C30 and QLQ-MY20)

The primary outcome of this study is HRQoL after the 3-month supervised exercise intervention compared with the waitlist control. HRQoL will be measured using the overall HRQoL summary score for the core HRQoL questionnaire of the European Organisation for Research and Treatment of Cancer Quality of Life Questionnaire (EORTC QLQ-C30, version 3.0) [46]. The EORTC QLQ-C30 is a widely used and well-validated cancer-specific instrument [3] with good psychometric properties in solid tumors [47,48]. It has acceptable reliability and validity in MM (Cronbach’s α = 0.70–0.92, except role function = 0.54), with an excellent ability to discriminate between patients in different objective disease states and a high responsiveness to changes in patients’ clinical status over time [3,49]. In a recent Delphi analysis, consensus was reached to collect patient-reported outcomes using the EORTC QLQ-C30 in patients with MM [50]. The minimal important difference (MID), defined as the smallest change in a HRQoL score considered important to patients that would lead the patient or clinician to consider a change in therapy, will be based on those estimated for individual scales of the QLQ-C30 in patients with MM [51].

The EORTC QLQ-C30 summary score encompasses all symptom (e.g., fatigue, pain) and function domains (e.g., emotional and social functioning) assessed by the QLQ-C30. The summary score is a strong prognostic factor for overall survival above and beyond that provided by clinical and sociodemographic variables for patients with MM [7]. The summary score also appears to have more prognostic value than the global QoL, physical functioning, or any other scale within the QLQ-C30 [7].

The European Organisation for Research and Treatment of Cancer Quality of Life Questionnaire Multiple Myeloma module (EORTC QLQ-MY20) is a reliable and valid instrument, recommended as a supplement to the QLQ-C30 instrument in patients with MM (Cronbach’s α = 0.70–0.92) [52]. As with the QLQ-C30, QLQ-MY20 domain scores are averaged and transformed linearly to a score ranging from 0–100. A high score for disease symptoms and side effects of treatment represents a high level of symptomatology or problems, whereas a high score for future perspective and body image represents better outcomes.

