#### 3.3.3. Adverse and Serious Adverse Events

Safety of the intervention will be measured through reporting adverse and serious adverse events. The trial AEP will record at each testing and supervised training session whether an adverse event has occurred and, if so, the AEP will provide details to the governing ethics committee. Events at unsupervised sessions will require self-report by the participant to the trial AEP. Adverse events will be reported to the study clinicians and the participant’s treating doctor for further decisions on safety and any required investigations. Trial insurance provided through the sponsor, The University of Queensland, includes provision for post-trial care if required.

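### A health event that stops exercise for over a month takes the participant out of the trial, not only out of exercise, which risks selective and possibly unequal loss of the 3-month HRQoL score

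*Protocol article*

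**What the plan says.** Section 2.2 (Participants) sets the rule: "Individual participants will be discontinued from the trial, in agreement with their doctor where appropriate, if any major surgery or health condition arises". The rule is limited to events lasting long enough to keep the person from exercising safely for over a month. The same sentence gives withdrawal of consent as the other route out, with the same consequence. The rule is worded for all participants, not for one arm.

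Section 3.1 defines the endpoint: "The primary outcome of this study is HRQoL after the 3-month supervised exercise intervention compared with the waitlist control". It is the summary score of the patient-completed QLQ-C30.

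Section 5 covers incomplete data: "Incomplete data and missing values will primarily be managed using intention-to-treat analyses, using a 70% cut-point for adherence". It adds "To ensure the robustness of the findings, a secondary sensitivity analysis will be performed" and "The number of participants who provide data at each timepoint will be reported, with reasons as to why participants did not attend". The content of the sensitivity analysis is not described.

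On detection of health events, Section 3.3.3 says: "The trial AEP will record at each testing and supervised training session whether an adverse event has occurred". Section 2.5 (Stepped Down Supervision Approach) gives exercise participants (EX) two supervised sessions a week for twelve weeks. Section 2.1 describes waitlist participants (WT) over the same period only as keeping to their usual activity. Under Table 1 and its first footnote, they repeat the baseline battery after three months.

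**The concern.** A participant can become unfit to exercise and still answer a questionnaire. The rule does not allow for this: the event that ends the intervention also ends participation, and with it the 3-month score. Major surgery or a lasting health condition plausibly lowers the QLQ-C30 summary score, which covers symptoms and functioning, so the missing scores would tend to be the low ones.

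This sits in tension with the intention-to-treat approach of Section 5, because the plan itself creates missing outcomes among randomised participants for a reason arising after randomisation. It also narrows the population. Section 7 presents inclusion of all disease stages, particularly relapsed disease, as a strength, yet a participant with a serious complication may leave before the outcome is measured. Safety follow-up and the 12-month maintenance question lose the same people.

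If removals were more frequent in EX, its mean would be taken over those who stayed well while similar WT participants still counted, and the comparison would favour exercise.

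**Working it through.** **Plan's own figure.** Section 5 needs 22 per group and allows 25% dropout: 22 / 0.75 = 29.3, so 30 per arm and 60 in total. The stated 60 is reproduced. After 25% loss, 60 × 0.75 = 45 remain, against 44 required. The allowance therefore covers lost numbers, but it does nothing about who is lost.

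**Why the model does not repair it.** Someone removed before 3 months contributes a baseline score only. The mixed model and baseline adjustment in Section 5 can account for the part of the deficit already visible at baseline, but not for a fall caused by a later event.

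**Size of the possible bias.** Let p be the proportion of an arm removed under the rule. Let D be the number of points by which those removed would have scored below those kept at 3 months, beyond what baseline explains. D is taken as equal in the two arms.

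- If K is the mean of those kept, the full-arm mean is (1 − p)·K + p·(K − D) = K − p·D.
- The mean of those observed is K, so it is too high by p·D.
- Bias in the EX − WT difference = D × (p_EX − p_WT).

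The documents give neither p nor D, so the values below are assumptions.

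| Removed EX | Removed WT | Excess in EX | D = 10 | D = 20 | D = 30 |
|---|---|---|---|---|---|
| 25% | 25% | 0 points | 0 | 0 | 0 |
| 10% | 5% | 5 points | 0.5 | 1.0 | 1.5 |
| 20% | 10% | 10 points | 1.0 | 2.0 | 3.0 |
| 20% | 5% | 15 points | 1.5 | 3.0 | 4.5 |
| 25% | 10% | 15 points | 1.5 | 3.0 | 4.5 |

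(Excess is in percentage points; the last three columns are QLQ-C30 points in favour of exercise.)

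Against the 6.7-point target, 0.5 / 6.7 = 7% and 4.5 / 6.7 = 67%. If removal were higher in WT, the sign would reverse.

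**Is unequal removal plausible?** Over 12 weeks EX has 2 × 12 = 24 supervised contacts at which events are recorded. For WT the article describes no scheduled contact between baseline and the 3-month test. The same event could therefore come to staff attention earlier in EX. This is an inference from the contact schedule; the article does not say it.

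**The case against.** **The rule is neutral between arms.** This stands. A reader might infer that it removes the sickest mainly from the exercise arm and so does bias the result. The article does not support that: no removal rate by arm is given, and recording an event at a session is not the same as removal. Events serious enough to meet the rule may surface without twice-weekly contact. WT participants also start the programme after week 12, so their fitness to exercise matters too.

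**WT scores might be lost as well.** This also stands. One might assume that a WT participant with such an event would still give a score at 3 months. Section 3 places all testing in the university laboratories, and Table 1 puts the questionnaire alongside fitness, scanning and strength tests. A WT participant after surgery could miss that visit. The differential loss could be small.

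**The worst case is easily overstated.** Multiplying the full 25% dropout by a 20-point deficit gives 5 points, or 75% of the target. That assigns all dropout in EX to this one rule and assumes no loss in WT. Section 5 gives 25% overall, not by arm or cause, and Section 2.2 itself names consent withdrawal as another route.

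**Intention-to-treat is about analysis by randomised arm.** This is fair, so tension is the right word rather than contradiction. Reporting numbers and reasons, and running a sensitivity analysis, would disclose the loss and perhaps probe it, but would not recover the scores.

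**The full protocol may add follow-up procedures.** It may. But the article does not leave the point open: it states that these participants leave the trial, on the same footing as those who withdraw consent.

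**Conclusion.** The concern holds in a limited form. The stated rule ends trial participation for a health-related reason, and no part of the article keeps collecting the primary outcome afterwards. It therefore risks selective loss of the 3-month QLQ-C30 score, and that loss may differ between arms because contact differs.

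The bias is 0 if similar participants are removed equally from both arms, although the result then describes only those who stayed fit to exercise. It is about 0.5 to 4.5 points in favour of exercise if EX loses 5 to 15 percentage points more than WT and those removed would have scored 10 to 30 points lower. The formula is firm; the inputs are assumptions. That bias occurs, or that removal falls mainly on EX, cannot be concluded from the document.

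**What to change.** Leave the clinical criterion for stopping exercise as it is, and change only its consequence, from leaving the trial to leaving the exercise programme. Then state that:

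- the QLQ-C30 and QLQ-MY20 and adverse-event follow-up continue unless the participant withdraws consent to follow-up. Remote completion is allowed where attendance is not possible;
- the 3-month score has priority, because it carries the randomised comparison. Scores at 6 and 12 months serve the maintenance aim, since WT has begun exercising by then;
- all scores are analysed in the randomised arm;
- discontinuations of exercise and withdrawals from follow-up are reported separately, by arm and with reasons.

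No new WT enquiry at 3 months is needed. Table 1 already collects health history and disease status then, Section 3 documents changes in medical status and hospital admissions, and Section 3.3.3 records adverse events at testing sessions.

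The cost is minor wording in the protocol and consent form and a few remote questionnaires. The sample size stays at 60. The estimated effect may be smaller, because participants who could not complete the programme would be counted.
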